#### Strategies to improve adherence to interventions and criteria for discontinuing or modifying allocated interventions

2.3.2

Please refer to Appendix S1.

### Outcomes

2.4

#### Primary endpoint

2.4.1

This study will compare the diversity of the intestinal microbiome in infants with risk for atopic diseases in Group A versus Group B after the introduction of solids (time point V5). The diversity will be measured via alpha diversity calculations; the Shannon diversity, the Gini‐Simpson index, or the evenness will be calculated.^29^

#### Main secondary endpoints (for further endpoints, please see Appendix S1)

2.4.2

Compliance assessment/adherence of parents/caregivers conducting pre‐chewing via questionnaire on performance and frequency: query on a weekly basis, if performed daily; 4–7 times per week; <3 times/week (compliance defined as at least 4 days/week ≙ 57%)Composition of the oral microbiome and frequency of infant caries by 1 year of age (V5) according to the International Caries Detection and Assessment System (ICDAS, a clinical scoring system allowing detection and assessment of caries lesions and caries experience^30^)Frequency of IgE‐mediated food allergies to at least one of the four foods (hen's egg, cow's milk, peanut, hazelnut) after intervention by 1 year of age (V5) between Groups A and BAllergen‐specific IgE and IgG4 to hen's egg, cow's milk, peanut, hazelnut, Ara h 2, Cor a 14, and wheat at V1 and V5 in comparison between groups.Cumulative occurrence (frequency and severity) of respiratory and gastrointestinal infections (including oral infections) in comparison between groups

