#### Intervention description

2.3.1

Mothers of both groups will be encouraged to continue breastfeeding while weaning foods are introduced stepwise to the infant's diet. Parents will decide in advance which group they would like to join, and—depending on the child's individual development—when first complementary foods are to be introduced (Figure 1). All participants will be informed equally regarding current feeding recommendations.^17^, ^21^

All Group A participants will visit the study site at five timepoints (V1–V5). Group B participants will visit the study site at two timepoints (V1 and V5). Blood samples will be collected at V1 and V5; SPT will be performed at V5 only. Samples for microbiome analysis will be taken at indicated visits. Telephone calls are scheduled 2 weeks after V1, V2, V3, and V4 (Group A) and 2 weeks after V1 as well as one interim phone call at week 12 (Group B).

All caregivers will be encouraged to keep a weekly diary recording frequency of pre‐chewing, tolerability, and palatability of solids introduction, as well as any adverse events, concomitant medication, and diet.

V0 (collection of stools + skin swabs) and V6 (enhanced diagnostic in sensitized subjects, including oral food challenges) are optional.

V5 solo consists only of V5 (and optional V6); participants will not have been enrolled before.

Group A – “Interventional/Pre‐chewing Group”: The mother (or one other previously determined caregiver) of an eligible infant will receive a sugar‐free ground biscuit once the infant starts eating complementary foods. The biscuit is ground to ensure homogeneity of the amount of included food proteins. These amounts will be increased by a factor of five in four stages, each lasting 6 weeks ±14 days, V1–V4 (Table 2). The actual amount of total protein of the allergenic food in the first dose at V1 (Table 2) starts slightly below calculated discrete ED05 values for the correspondent food allergens,^25^ which are 2.1 mg peanut protein, 3.5 mg hazelnut protein, 2.3 mg hen's egg protein, and 2.4 mg cow's milk protein. Further ingredients of the biscuit are wheat flour type 550 and margarine processed with rapeseed oil.

**TABLE 2 pai70147-tbl-0002:** Content of Peanut, Hazelnut, Hen's Egg, and Cow's Milk protein in the ground biscuit.

Group A	Visit 1–Visit 2	Visit 2–Visit 3	Visit 3–Visit 4	Visit 4–Visit 5/6

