### Statistical methods

3.3

Diversity of the microbiome (primary endpoint) will be assessed utilizing alpha diversity calculations.^29^ The two study groups are compared using this diversity parameter. Moreover, based on the alpha diversity, other diversity indices like the Shannon diversity, the Gini‐Simpson index, or the evenness will be evaluated. No sample size calculation was performed due to the exploratory study design. *N* = 50 subjects per group is regarded as appropriate in order of magnitude of the few other studies in the context of pre‐chewing/saliva contact and/or microbiome analysis.^37^, ^38^, ^39^

In our explorative study, the primary efficacy analysis will be based on the full analysis set (FAS) and a secondary analysis will also be performed on the per protocol population (PPS) to assess the sensitivity of the analysis to the choice of analysis set. All safety analyses will be based on the full analysis set (FAS). The analysis will be performed without imputation of missing values. The significance level will be set to 0.05 (two‐sided). All other analyses will be considered explorative.

Univariable and multivariable logistic regression models will be performed for secondary binary endpoints (e.g., one diagnosed food allergy, food specific sensitisation, indices on microbiome diversity calculations). The analysis of secondary continuous endpoints (e.g., SCORAD, compliance over time) is conducted using analysis of covariance (ANCOVA). Child's sex, birth mode, number of siblings, pets, and other factors will be considered as covariates. Analysis will be carried out with the FAS. Based on the intention‐to‐treat (ITT) principle, the patients are analyzed according to the study group in which they started in.

Several explorative subcohort analyses (e.g., on antibiotic intake, infections) will be performed for the primary endpoint to find possible associations between covariates and diversity of the intestinal microbiome.

Selected secondary endpoints will also be analyzed with the PPS. The PPS is a subset of the FAS defined without participants with repeated insufficient consumption of the study product, defined as consumption <4 times/week (57%). As a general strategy, missing data will not be imputed in this study.

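### The weekly compliance categories have no place for three times per week, and the per-protocol rule counts biscuit consumption, not pre-chewing

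*Protocol article*

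**What the plan says.** Section 2.4.2 (Main secondary endpoints) lists first "Compliance assessment/adherence of parents/caregivers conducting" pre-chewing. It is collected by questionnaire as "query on a weekly basis, if performed daily; 4–7 times per week; <3 times/week", with "compliance defined as at least 4 days/week ≙ 57" per cent.

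Section 3.3 (Statistical methods) makes the full analysis set (FAS) primary and uses the PPS as a secondary analysis, to see whether the result depends on the analysis set. It defines the PPS as follows: "The PPS is a subset of the FAS defined without participants with repeated insufficient consumption of the study product". Insufficient means fewer than 4 times per week, again given as 57%. Missing values are not imputed.

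Section 2.3.1 (Intervention description) gives the biscuit to Group A only, as one portion a day on at least four days a week. Group B introduces solids without pre-chewing. On the diary it says: "All caregivers will be encouraged to keep a weekly diary recording frequency of" pre-chewing, among other items. V5-solo participants join Group B's last visit without earlier enrolment.

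The Discussion describes the primary objective as whether passing on pre-chewed food influences the infant's microbiome. It names the practicability and acceptance of pre-chewing, including how often it is done, as something the trial will assess.

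**The concern.** There are two separate defects.

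The first is in the response categories. They should place every weekly frequency in exactly one box and split cleanly at the compliance cut. They do neither, and the hole lies directly below the cut. Three is the nearest shortfall from the instructed minimum of four, so it is a plausible answer. A caregiver at three has to tick a compliant box, tick a box that is literally wrong, or leave the item blank.

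The second is in what the PPS counts. A per-protocol analysis is informative when it keeps those who received the exposure under study. Here the exposure of interest is pre-chewing, but the stated exclusion concerns consumption of the product. Because Group B has no product, the rule also acts on one arm only, in a trial where parents choose their group. At stake are the accuracy of the adherence endpoint near its threshold and what a PPS result can say about the primary comparison of diversity at V5.

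**Working it through.** **Threshold.** 4/7 = 57.1%, which reproduces the stated 57%. The next value down is 3/7 = 42.9%.

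**Categories.** Each weekly frequency against the three boxes in Section 2.4.2 and the cut of at least 4:

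| Times per week | Box that fits | Status by the definition |
|---|---|---|
| 0, 1, 2 | <3 | non-compliant |
| 3 | none | non-compliant |
| 4, 5, 6 | 4–7 | compliant |
| 7 | daily and 4–7 | compliant |

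The double fit at 7 does not move anyone across the cut. For a week at three, ticking <3 gives the right status, ticking 4–7 gives the wrong one, and a blank is missing and not imputed.

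**PPS rule against the endpoint.** The feeding instruction (at least four), the compliance definition (at least 4 days) and the PPS cut-off (below 4 is insufficient) agree on the number. They differ in what is counted:

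- Section 2.4.2 counts pre-chewing.
- Section 3.3 counts consumption of the study product.

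Section 2.3.1 tells caregivers not to pre-chew in certain circumstances, such as an infection or an open wound in the mouth, so the two counts can differ. Under the stated rule:

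| Infant | PPS under the stated rule |
|---|---|
| Group A, biscuit at least 4 times a week, pre-chewed | stays |
| Group A, biscuit at least 4 times a week, not pre-chewed | stays |
| Group A, biscuit repeatedly below 4 times a week | removed |
| Group B, not pre-chewed | stays |
| Group B, pre-chewed despite the group description | stays |

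**When one-arm exclusion matters.** Suppose there is no true effect, the least adherent fraction q of Group A is removed, and adherence correlates rho with diversity. With φ the standard normal density and z_q its q-quantile, the bias is rho × φ(z_q)/(1 − q) in SD units. The test uses SE = sqrt(1/50 + 1/n_A) with n_A = 50(1 − q), two-sided at 0.05. The article gives neither q nor rho, so both are assumptions:

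- rho = 0, any q: bias 0, type I error 0.050.
- q = 10%, rho = 0.1: 0.1 × 0.175/0.9 = 0.02 SD; type I error 0.051.
- q = 20%, rho = 0.3: 0.3 × 0.280/0.8 = 0.11 SD; SE = sqrt(1/50 + 1/40) = 0.212; type I error 0.078.
- q = 40%, rho = 0.5: 0.5 × 0.386/0.6 = 0.32 SD; SE = sqrt(1/50 + 1/30) = 0.231; type I error 0.286.

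The range runs from nothing to substantial. It shows the condition under which the check fails and does not estimate what will happen in this trial.

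**The case against.** Much can be said for the plan. The questionnaire itself is not printed, the diary covers frequency of pre-chewing, and compliance is reviewed at Group A's phone calls, so exact counts may exist. That softens the first defect without removing it: the diary is only encouraged, the article does not say whether it holds counts or the same boxes, and the categories as printed are wrong.

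The FAS is primary, the trial is exploratory, and the Discussion openly concedes bias from self-chosen groups. Removing participants only from the arm that has a product is usual when the comparator has none. Consumption is also a legitimate part of adherence, because the intervention combines allergen introduction with pre-chewing. All of this stands. But counting pre-chewed biscuit portions would capture both parts, and consumption alone does not. Further PPS criteria may be in the full protocol, so the point here concerns only what the stated rule counts.

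Four stronger readings are tempting and not supported:

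- A reader might infer that the PPS rule is built on the faulty categories. It has its own complete cut-off and shares only the number four.
- A reader might infer that every week at three is misrecorded. Ticking <3 gives the right status.
- A reader might infer that the PPS analysis does mislead. That needs a link between adherence and diversity, and the article gives no information on one.
- Section 3.3 says "The analysis of secondary continuous endpoints (e.g., SCORAD, compliance over time) is conducted using analysis of covariance (ANCOVA"), and a reader might infer a between-group ANCOVA of something only Group A does. The text does not say between groups; a percentage or mean frequency modelled within Group A would fit it.

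**Conclusion.** The point holds in two limited parts. The category gap at three is certain from the printed text and affects one of eight possible weekly values, the one just below the cut. Its effect on the compliance rate depends on how many weeks fall there and which box is ticked, neither of which the article gives. The overlap at seven is cosmetic.

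The mismatch in the PPS rule is also plain on the page. Its consequence is conditional: the PPS can mislead if adherence is related to diversity for reasons other than the intervention, and one-arm exclusion does no harm if it is not. The primary FAS analysis is untouched. This should be corrected because the correction is easy and the endpoint is listed first among the main secondaries; it does not threaten the trial's main comparison.

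**What to change.** **Compliance item.** Record the number of days per week with a pre-chewed portion, 0 to 7. If boxes are preferred, use 7 / 4–6 / 0–3. The cut of at least 4 and the 57% do not change.

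**Weeks already collected.** State a mapping: daily and 4–7 as compliant, <3 as non-compliant, and blanks resolved from the diary where it holds a count, otherwise missing. Say that some old 4–7 answers may be weeks at three.

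**PPS.** Define adherence in Group A on pre-chewed portions per week, keeping the existing cut-off. Exclude enrolled Group B infants whose diary shows pre-chewing. State that V5-solo participants have no prior diary, so this check cannot cover them. Report the PPS result as a comparison with exclusions mainly in one arm, with the number removed from each group.

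**Cost.** One questionnaire or diary item, a few sentences of PPS wording and the mapping. The article notes amendments during the trial, so the item may no longer be changeable for families already enrolled; for them only the mapping and the PPS wording apply.

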### Participant timeline

2.5

Please see Figure 1 and Table 3. Please refer also to Appensix S1 for correspondent information.

### Recruitment

2.6

Please refer to Appendix S1 for recruitment information.

## METHODS: DATA COLLECTION, MANAGEMENT, AND ANALYSIS

3

### Data collection methods

3.1

#### Clinical data

3.1.1

Written informed consent must be obtained at the screening visit, and inclusion and exclusion criteria will be reviewed. Information on demographics, subjects/family characteristics, relevant medical history, concomitant medication, and nutrition will be recorded. Questions on feeding habits, environmental factors, and family history will be repeated via a comprehensive questionnaire at different timepoints (V0, V1, and V5). Physical examination (including weight, and length measurements as well as SCORAD and EASI score when applicable^31^, ^32^, ^33^, ^34^) of the child will be carried out at every study visit besides V0, and information on individual use of pacifiers, thumb sucking, or other microbiome‐influencing aspects of personal hygiene will be collected using a routinely applied questionnaire at every study visit.

#### Stool and saliva samples for microbiome analysis

3.1.2

Stool samples and skin swabs will be collected from the infants and the mothers at V0, V1, V3, and V5. The stool samples will be taken at home by the parents before the site visits. Collection of stool samples will be done using DNA/RNA Shield Fecal Collection Tubes (Zymo Research, Irvine, CA, USA). Our approach will be based on extraction and sequencing of V3–V4 regions of the 16SrRNA. The sequencing will be performed on a MiSeq platform (Illumina, San Diego, CA, USA) using V2 reagents (Illumina, San Diego, CA, USA). The sequencing length will be 2 × 250 bp. The diversity of the intestinal microbiome will be measured via alpha diversity calculations, which enable the comparison of the two groups with differing diets. Moreover, alpha diversity is a basis for other diversity calculations like the Shannon diversity, the Gini‐Simpson index, or the evenness, which will also be calculated.

Saliva samples (swab of the oral mucosa) will be collected from the infant and caregivers at V1 and at V5. Saliva samples will be obtained using Zymo Swabs (DNA/RNA Shield; Zymo Research, Irvine, CA, USA).

#### Dental examination using telediagnostics

3.1.3

All (pre‐chewing) caregivers will receive a dental examination at V1 using telediagnostics. Caries lesions as well as missing and filled teeth (DMFT Index) will be assessed using the WHO protocol. Caries lesions will be assessed visually according to ICDAS without assessment of ICDAS code 1 (as drying the teeth will not be feasible using tele‐diagnostics).^30^ In case of existing caries lesions, the parent will be asked to treat corresponding lesions before starting the practice of pre‐chewing and will be invited for remaining V1 procedures and initiation of pre‐chewing after dental treatment only. The child's dental chart will be examined at V5 (end of study). Telediagnostics will be provided by an experienced dentist specifically trained upfront.

Please note the Appendix S1 for Continuation of *Clinical Assessment Methods and Clinical Outcome Definitions* on
Skin swabs for microbiome analysisAllergy diagnostic including Skin Prick Test (SPT) and blood samplingDouble‐Blind Placebo‐Controlled Food Challenge (DBPCFC)^35^
Skin Barrier Permeability^36^

### Data management

3.2

Please refer to Appendix S1 for information on data management.

### Statistical methods

3.3

Diversity of the microbiome (primary endpoint) will be assessed utilizing alpha diversity calculations.^29^ The two study groups are compared using this diversity parameter. Moreover, based on the alpha diversity, other diversity indices like the Shannon diversity, the Gini‐Simpson index, or the evenness will be evaluated. No sample size calculation was performed due to the exploratory study design. *N* = 50 subjects per group is regarded as appropriate in order of magnitude of the few other studies in the context of pre‐chewing/saliva contact and/or microbiome analysis.^37^, ^38^, ^39^

In our explorative study, the primary efficacy analysis will be based on the full analysis set (FAS) and a secondary analysis will also be performed on the per protocol population (PPS) to assess the sensitivity of the analysis to the choice of analysis set. All safety analyses will be based on the full analysis set (FAS). The analysis will be performed without imputation of missing values. The significance level will be set to 0.05 (two‐sided). All other analyses will be considered explorative.

Univariable and multivariable logistic regression models will be performed for secondary binary endpoints (e.g., one diagnosed food allergy, food specific sensitisation, indices on microbiome diversity calculations). The analysis of secondary continuous endpoints (e.g., SCORAD, compliance over time) is conducted using analysis of covariance (ANCOVA). Child's sex, birth mode, number of siblings, pets, and other factors will be considered as covariates. Analysis will be carried out with the FAS. Based on the intention‐to‐treat (ITT) principle, the patients are analyzed according to the study group in which they started in.

Several explorative subcohort analyses (e.g., on antibiotic intake, infections) will be performed for the primary endpoint to find possible associations between covariates and diversity of the intestinal microbiome.

Selected secondary endpoints will also be analyzed with the PPS. The PPS is a subset of the FAS defined without participants with repeated insufficient consumption of the study product, defined as consumption <4 times/week (57%). As a general strategy, missing data will not be imputed in this study.

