Our biggest concern is that we will not recruit enough caregivers who choose to take part in the pre‐chewing group. Premastication is not well known and is viewed rather critically in Germany.^46^ However, as our primary objective is to analyze whether the transmission of pre‐chewed foods for solid introduction has any influence on the infant's microbiome, we decided to choose an open‐study design despite the various limitations and the bias by the open selection of study groups. As data on the effect of pre‐chewing on microbiome analysis is rare, the estimated power is based on current publications that have in some way addressed the transfer of saliva,^38^ analyzed the oral microbiota in relation to allergy development,^39^ or analyzed its composition after premastication.^37^ Although the open design and the question of power are the biggest limitations, these factors also strengthen the outstanding position of this trial. This study will allow us to not only analyze the changes in microbiome composition (oral, skin, intestinal) over time, but also the influence of premastication for the first time. This exploratory first approach is built up carefully in order to identify danger signals early on. But we can also perhaps show that the exchange of parental saliva on the child is not “harmful” per se, but can also do “good”.

As final remark, it should be emphasized that this open trial will not be suitable for drawing recommendations on the prevention of cow's milk, hen's egg, peanut, and/or hazelnut allergies based on the outlined approach. This is particularly the case since no placebo biscuit (ground biscuit without the four food allergens) with or without pre‐chewing is included. Rather, the practicability and acceptance of the old feeding practice of premastication (if done at all, when and how often it is carried out) and its impact on the infant's microbiome will be assessed. Nevertheless, this study is a first step in pursuing the hypotheses on this combined approach and a potential utilization of premastication as an “allergy‐protective” puzzle piece for food allergy prevention.

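### Parents choose the study group, yet the plan commits to no covariate or baseline adjustment of the primary comparison of V5 diversity

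*Protocol article*

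**What the plan says.** **Allocation.** Protocol article, 2.3.1 Intervention description: "Parents will decide in advance which group they would like to join". Section 1.2 Objectives calls the comparison non-randomised, but words the primary objective as the impact of feeding habits on diversity.

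**Primary endpoint.** Section 2.4.1 compares intestinal diversity "in Group A versus Group B after the introduction of solids (time point V5"). It is a value at one time point.

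**Primary analysis.** Section 3.3 Statistical methods: "The two study groups are compared using this diversity parameter". No model, covariate or baseline term is attached. On the test level, the section says "The significance level will be set to 0.05" (two-sided) and calls all other analyses explorative.

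**Where adjustment is named.** A later paragraph of 3.3 assigns univariable and multivariable logistic regression to secondary binary endpoints, and continues: "The analysis of secondary continuous endpoints (e.g., SCORAD, compliance over time) is conducted using analysis of covariance (ANCOVA"). The next sentence lists sex, birth mode, siblings, pets and unspecified further factors as covariates. A separate paragraph gives the primary endpoint exploratory subcohort analyses, for example by antibiotic intake, to look for associations between covariates and diversity.

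**Baseline data.** Section 3.1.2 and Table 3 schedule infant stool at V1 in both enrolled groups. Parents take it at home before the visit. The first biscuit portion is given at the V1 visit (Figure 1 legend).

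**Acknowledged limitation.** The Discussion says the open design was chosen "despite the various limitations and the bias by the open selection of study groups".

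**The concern.** Parents who choose premastication may well differ from those who do not in birth mode, milk feeding, household, pets, hygiene and age at first solids. Section 1.1.1 itself names several of these as factors in allergy and says that early environmental experience is reflected in the gut microbiome. A crude V5 contrast adds any such differences to whatever the feeding practice does.

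In a non-randomised comparison, adjustment for pre-intervention differences is the main analytic defence. Here the text attaches that defence to the secondary endpoints, and does not attach it to the one comparison singled out as primary. Followed as written, the analysis would not support a statement about impact. It would also leave V1 diversity out of the primary comparison, although V1 diversity could both reduce bias and add precision.

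**Working it through.** **Step 1: reading the text.** Four parts of 3.3 bear on the question.

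| Part of 3.3 | Endpoint named | Role of covariates |
|---|---|---|
| Opening paragraph | Primary | None stated; groups are compared |
| Regression and ANCOVA sentences | Secondary binary, secondary continuous | Models that can adjust |
| Covariate sentence, directly after | None named | To be considered; list is open-ended |
| Subcohort paragraph | Primary | Exploratory associations with diversity |

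The last row does not adjust A versus B: it looks at how diversity varies with a covariate. Diversity indices are also listed for logistic regression, but there as secondary binary endpoints.

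**Step 2: the sample size.** N = 50 "subjects per group is regarded as appropriate in order of magnitude of the few other studies". It cannot be reproduced, because "No sample size calculation was performed due to the exploratory study design". No effect size, SD or power is given, so everything below is in SD units.

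**Step 3: crude test under selection alone.** Inputs from the plan: n = 50 per group, two-sided 0.05. Assumed: no feeding effect and a net selection shift b, in SD units.

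- SE = sqrt(2/50) = 0.20 SD.
- Rejection probability = 1 − Φ(1.96 − b/SE) + Φ(−1.96 − b/SE).

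| b (SD, assumed) | b/SE | Normal approximation | t-test, 98 df |
|---|---|---|---|
| 0 | 0 | 5% | 5% |
| 0.2 | 1.0 | 17.0% | 16.8% |
| 0.3 | 1.5 | 32.3% | 31.8% |
| 0.4 | 2.0 | 51.6% | 50.8% |

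One way to reach 0.3 SD: three covariates, each differing by 20 percentage points between groups and each worth 0.5 SD in the same direction, give 3 × 0.20 × 0.5 = 0.30 SD. These values are assumed too.

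**Step 4: precision from V1.** The difference detectable with 80% power is 0.566 SD (t-test). With V1–V5 correlation r within groups (assumed), ANCOVA multiplies it by sqrt(1 − r²):

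- r = 0.2: 0.566 × 0.980 = 0.555 SD
- r = 0.5: 0.566 × 0.866 = 0.490 SD

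The gain is negligible at r = 0.2 and moderate at r = 0.5.

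**Step 5: what V1 adjustment does to bias.** Two assumed scenarios, both with no feeding effect (normal approximation):

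- *Selection acts only through the V1 level.* The crude V5 shift is r × B, where B is the V1 difference. From r = 0.3, B = 0.3 (shift 0.09) to r = 0.7, B = 0.5 (shift 0.35), the crude test rejects 7% to 42% of the time. ANCOVA on V1 returns this to 5%.
- *A 0.5 SD difference is present at both visits.* The crude test rejects 70.5% of the time. ANCOVA leaves a bias of 0.5 × (1 − r) with SE 0.20 × sqrt(1 − r²). For r = 0.3, 0.5 and 0.7 the bias is 0.35, 0.25 and 0.15 SD, and rejection is 45%, 30% and 18%.

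Baseline adjustment alone may therefore not be enough, which is why the other covariates are needed.

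**Step 6: age at the V5 stool.** V1 at 4–8 months (Figure 1 legend) plus 24 weeks (Table 3; 24/4.345 = 5.5 months) gives about 9.5 to 13.5 months. Section 2.3.1 places V5 in Group B around the first birthday. Age at sampling can therefore differ between groups.

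**The case against.** The strongest reply is that the article never says the primary contrast is crude. The covariate sentence is not restricted to secondary endpoints, and the sentences after it, on the full analysis set and on intention to treat, read like general rules. The article is an abridged protocol, and a full protocol or SAP may specify an adjusted model. This stands as far as it goes: a reader might infer that the plan rules out adjustment of the primary endpoint, and the text does not support that. What remains is not mere silence. The article does assign models and covariates, and it gives the primary endpoint a different and non-adjusting use of them.

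Four other stronger readings also fail.

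- *The covariate list leaves out age, feeding and centre.* The list is open-ended and could include them. Antibiotic intake is named, though only for subcohorts.
- *The V1 sample is unused, or is the only check on baseline comparability.* The Discussion foresees analysis of microbiome changes over time. Optional V0 stool and V1 family, nutrition, hygiene and medication data also bear on comparability. The point concerns the primary comparison only.
- *The investigators overlook selection.* They name the bias, call the study exploratory, disclaim prevention recommendations and add V5 solo as a reference not previously informed about premastication. None of this adjusts the contrast, and V5 solo does not address self-selection into Group A.
- *The trial has a false-positive rate of 17% to 51%.* The documents give neither a selection shift nor a V1–V5 correlation. Those figures show what could happen.

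**Conclusion.** The concern holds in a limited form. With parent-chosen groups and an objective worded as impact, 3.3 commits to no covariate or baseline adjustment of the primary contrast, while it places the adjusting models with the secondary endpoints. That the analysis is crude is inferred from this placement; at best the text is ambiguous on the main protection this design has.

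The consequence could be large: about 17%, 32% or 51% rejection instead of 5% for selection shifts of 0.2, 0.3 or 0.4 SD, with 50 per group and no feeding effect. The shifts are wholly assumed. The exploratory label and the acknowledged bias temper the claim, but they do not make a crude difference interpretable as an effect of feeding. Nor would adjustment guarantee that: it reduces selection bias and cannot be shown to remove it.

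**What to change.** State in the protocol or SAP that the primary analysis is a linear model (ANCOVA) of V5 diversity, as a continuous variable, on group, adjusted for:

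- V1 stool diversity
- age at the V5 stool
- centre
- a short pre-specified set of recorded pre-intervention covariates: birth mode, feeding status at V1, siblings, pets and antibiotics before V1

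Report the adjusted difference with its 95% confidence interval as the primary result and the crude difference as supportive. Keep V5 solo infants out of this model, since they have no V1 sample, and analyse them separately as the additional reference group. Describe the result as an adjusted association, and say that selection bias may remain.

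**Cost.** Mainly wording, because the V1 stool and the relevant histories are already scheduled in both enrolled groups. The model uses about 8 of roughly 98 degrees of freedom. The larger cost is that infants with a missing V1 stool or covariate drop out, since nothing is imputed. Their number should be reported by group.
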